### Recruitment

The trial will enroll 90 participants, allocating 45 to each arm. Allowing for 15% attrition, this sample provides 90% power to detect a treatment effect at T1, assuming an independent samples 2-tailed *t* test, an *α* level of .05, and Cohen *d* of 0.75. The target size also accords with comparable 2-arm VR intervention studies [16].

The first participant was enrolled in March 2026. The study will recruit participants from various settings in Hong Kong, including middle schools, tertiary institutions, and community centers. Adequate participant enrollment will be facilitated through partnerships with collaborating institutions, which will post digital flyers and promotional videos on their social-media platforms to reach the target population. The participants’ inclusion criteria were as follows: youth aged 15 to 25 years with a score of 25 or higher on the Social Phobia Inventory (SPIN). The exclusion criteria were as follows: (1) inability to attempt a baseline assessment (eg, due to being unpermitted to leave a psychiatric ward); (2) photosensitive epilepsy or significant visual, auditory, or balance impairment; (3) currently receiving another intensive psychological intervention; (4) a history of neurological conditions (eg, traumatic brain injury); and (5) insufficient language proficiency to understand the intervention requirements. In this trial, any endorsement of suicidal ideation will trigger crisis intervention procedures. Participants will be promptly flagged, and a trained clinician will notify the school or guardian to ensure appropriate safety measures are taken. School tutors or social workers familiar with students’ mental health will help identify participants unsuitable for the study, especially those whose conditions may be masked in self-report questionnaires. Participants will be recruited and screened online or offline, but will complete all interventions offline. Participants will be briefed through tutorial video clips demonstrating the research flow regarding intervention procedures, timing, and frequency.

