#### Intervention Design and VR Scenarios

The intervention comprises 6 sessions of 60 minutes each. This structure could be effective and practical for the target demographic in Hong Kong, considering the efficacy of brief interventions, challenges with longer program retention, and the need for adaptability to the local context [21]. There are 6 VR scenarios: a café, classroom, interview room, public bus, social gathering, and family gathering. Each scenario consists of 10 sequentially structured tasks, increasing in difficulty over time. For example, in a job interview scenario, task 1 involves the participant interacting with a friendly interviewer. Task 2 introduces a neutral, more serious interviewer. Task 3 features a foreign language–speaking interviewer, requiring the participant to respond in a nonnative language (eg, English). Before each task, participants will see an automated dashboard through the VR headset, providing background information and clear instructions on required actions, such as introducing themselves by saying, “Hello, my name is Chan Da Men.” To enhance engagement and support, the system monitors response time and, if no response is detected within 20 seconds, automatically displays assistance options, including taking a short break, requesting support from a psychologist, or extending response time. This structured approach ensures that participants receive gradual exposure, real-time guidance, and adaptive support, enhancing learning, confidence, and anxiety management in the VR intervention.

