#### Intervention Flow

##### Structure of Each Intervention Session

Before each of the 6 intervention sessions, participants can freely choose from the 6 available VR scenarios based on their personal preferences and therapeutic needs. Each session is structured into 3 key phases (intervention flowchart; Figure 3):

Warm-up (10‐20 min): in the first session, therapists introduce themselves, provide an overview of the 6-session intervention, explain procedures and safety precautions, and address participants’ questions and concerns to build rapport. From the second to the sixth session, therapists review the chosen scenario, reflect on the previous session, and conduct a homework check-in to reinforce learning and progress.VR intervention (30 min): participants move to a separate VR-equipped room, where they wear a VR headset and a smartwatch to track physiological indicators, while a camera records real-time responses for later video feedback analysis. During the 30-minute session, the intervention runs autonomously without therapist assistance. Therapists remain in a monitoring room, receiving real-time feedback on participants’ body movements, voice volume, reaction speed, and fluency, as well as physiological indicators (eg, heart rate and skin conductance). If needed, therapists are on standby to enter the participant’s room on request.Debriefing (20 min): after the VR session, participants and therapists review the experience using video feedback and physiological data, identifying specific challenges, such as self-focused attention or cognitive distortions contributing to social anxiety. Therapists introduce coping strategies, such as deep breathing, to help manage anxiety in real-world situations. Before concluding the session, participants receive simple homework assignments, such as practicing breathing exercises in daily social interactions to reinforce learning and real-life application.

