##### Intervention Feature 1: Wearable Watch for Real-Time Biological Data Collection

To enhance real-time monitoring of participants’ mental states during the intervention, a commercially available wearable health-monitoring device will be used to collect physiological indicators, including: (1) electrodermal activity (EDA), which reflects changes in skin conductance and indicates levels of physiological arousal and emotional responses; and (2) heart rate variability (HRV), which measures variations in heartbeats associated with stress and emotional regulation. These physiological markers offer objective indicators of anxiety and emotional responses during VR-based exposure tasks.

The collected data will be transmitted in real-time to the back-end control panel (CP), allowing the research team to monitor participants’ anxiety responses during different VR scenarios. If the system detects elevated physiological responses (eg, increased EDA or decreased HRV) during a specific VR task, it signals that the participant may be experiencing heightened anxiety. The biological data will be reviewed postsession with the counseling psychologist. During follow-up discussions, the CP will explore the participant’s experience, validate their emotional responses, and help them develop personalized coping strategies based on their reactions.

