##### Intervention Feature 2: AI-Driven Adaptive Support and Ethical Safeguards

During sessions, AI-driven interactive support was provided through Doubao (developed by ByteDance), an AI-powered large language model used in this study primarily for speech recognition and response detection. Based on predefined indicators such as task progression, response delay, and physiological arousal patterns, the system may provide brief and standardized prompts. If signs of frustration, distress, elevated arousal, or prolonged nonresponse are detected, the AI adjusts its approach by offering reassurance, motivational feedback, or brief reminders to use breathing or grounding strategies introduced by the therapist. The AI component is used as a lightweight supportive function; it does not provide diagnoses, make clinical decisions, assess risk independently, or replace therapist judgment. Moreover, after each VR session, Doubao AI generates a personalized postsession report summarizing the participant’s emotional and physiological responses, as well as task completion. The report highlights moments of peak anxiety and recommendations for the next session, including areas for improvement and potential adjustments to intervention difficulty or pacing. Any AI-generated feedback used in debriefing will be reviewed by the therapist, who will decide whether and how to incorporate it into the session discussion. Prompts and feedback templates will be reviewed by the research team to ensure that they are clinically appropriate, nonjudgmental, and consistent with the intervention manual. The back-end code and implementation details can be made available upon reasonable request.

To protect data privacy, identifiable participant information will not be included in AI-generated summaries. Study data will be coded using participant IDs, and access to identifiable data will be restricted to authorized research personnel. Data transmission and storage will follow the approved data security procedures described in the ethics application. Participants will be informed during the consent process that AI-supported feedback may be used as part of the intervention, the type of data involved, the purpose of the AI-generated feedback, and the limits of AI involvement.

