#### Physiological Data

HRV and EDA data collected during VR sessions will be analyzed using repeated-measures ANOVA to examine within-subject changes across sessions and between-group differences over time. For EDA, any fluctuation exceeding 2 SDs from the participant’s baseline, sustained within a 5-second window before and after the peak, will be flagged as an arousal event. These events will be quantified per session and used as indicators of physiological reactivity. Their frequency and timing will be explored in relation to session content and subjective distress and may serve as predictors or correlates of treatment engagement and emotional processing.

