#### Secondary Analyses

A similar linear mixed effects modeling approach will be used for secondary outcomes, including depressive symptoms measured by the PHQ-9. Exploratory analyses will examine adherence indicators, including the number of sessions attended, task completion, and homework completion. Where appropriate, adherence may be examined as a predictor or moderator of symptom change. Physiological indicators, including HRV and EDA, will be analyzed descriptively and, where data quality permits, using repeated-measures models to explore within-participant changes across sessions and associations with subjective outcomes.

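### The HRV and EDA session trend carries no term for the self-chosen scenario, so if scenario or difficulty drifts over the 6 sessions it mixes changed response with changed stimulus

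*Protocol article*

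**What the plan says.** Physiological Data names both the method and its target: "HRV and EDA data collected during VR sessions will be analyzed using repeated-measures ANOVA to examine within-subject changes across sessions". No scenario or task-level factor is mentioned. Four other places bear on this.

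- *Structure of Each Intervention Session*: before each of the 6 sessions, "participants can freely choose from the 6 available VR scenarios based on their personal preferences and therapeutic needs".
- *Intervention Design and VR Scenarios*: "Each scenario consists of 10 sequentially structured tasks, increasing in difficulty over time".
- *Intervention Feature 2*: the report generated after a session can contain "recommendations for the next session, including areas for improvement and potential adjustments to intervention difficulty or pacing".
- *Intervention Feature 1*, on the meaning of the signals: "These physiological markers offer objective indicators of anxiety and emotional responses during VR-based exposure tasks".

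Two statements soften the picture. Physiological Data adds, for EDA arousal events, that "Their frequency and timing will be explored in relation to session content and subjective distress". Secondary Analyses describes the same data more loosely: descriptive summaries and, if the data are good enough, an analysis "using repeated-measures models to explore within-participant changes across sessions and associations with subjective outcomes".

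**The concern.** A trend over sessions reads naturally as a change in the person only if the stimulus stays comparable or varies without direction. Here the stimulus may change for three reasons: the participant's choice, the grading of tasks, and advice on difficulty after each session. None of these is fixed or counterbalanced against session number.

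Since the article treats HRV and EDA as indicators of anxiety, a falling trend invites the conclusion that participants became less anxious, when some may simply have moved to easier settings. A flat trend could equally hide real habituation offset by harder tasks. At stake is the interpretation of an exploratory result. None of the article's three hypotheses concerns physiology, and the SPIN analysis does not use these data.

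**Working it through.** **The plan's own figures.** The article gives no effect size, variance or scenario-specific arousal level for HRV or EDA, so there is no figure on this point to reproduce. Its only design figure is the SPIN power. From Recruitment, "The trial will enroll 90 participants, allocating 45 to each arm", with 15% attrition: 45 × 0.85 = 38.25 evaluable per arm. A two-sided t test with d = 0.75 and alpha 0.05 then has power 0.899, which agrees with the stated 90%. The point does not depend on it; it only supplies the 38 VR participants used below.

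**Precision of the session trend.** Assumptions: 38 participants, 6 sessions, residual within-person SD 1, no between-person variation in slope.

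- Centred sessions: sum of squares = 2 × (2.5² + 1.5² + 0.5²) = 17.5.
- SE of slope = 1/√(38 × 17.5) = 0.0388 SD per session.
- SE of the session 1 to 6 change = 5 × 0.0388 = 0.194 SD.

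**Shift from drift in scenario.** Assume no true change in response and no drift in task level. Let scenario means span R SD, and let a net share p of participants move by session 6 from an even mix to the least or most arousing scenario. The change shifts by p × R/2, in either direction.

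| p | R = 0.5 | R = 1 | R = 2 |
|---|---|---|---|
| 0 | 0 | 0 | 0 |
| 25% | 0.06 | 0.13 | 0.25 |
| 50% | 0.13 | 0.25 | 0.50 |
| 75% | 0.19 | 0.38 | 0.75 |

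The smallest non-zero entry is 0.0625/0.194 = 0.3 SE; the largest is 0.75/0.194 = 3.9 SE. If slopes also vary between people with SD 0.2 per session, the SE of the change is 5 × √((1/17.5 + 0.04)/38) = 0.253, and the largest shift is 0.75/0.253 = 3.0 SE. In simulation (3000 runs per non-zero case) the unadjusted change followed the table. With scenario in the model it lay between −0.009 and +0.006 SD. That recovery is built in, because scenario was the only cause of drift simulated.

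**Drift in difficulty.** In a separate simulation (4000 runs, also 38 participants), difficulty added 0.1 to 0.2 SD per step, rose by one step each session, and the response did not change. The session trend was significant in 70% to 99.8% of runs, or 37% to 91% when choice ran only loosely from easy to hard. When true habituation of 0.1 or 0.2 SD per session was offset by an equal difficulty effect in fixed order, the mean trend was zero and about 5% to 6% of runs were significant. With neither effect, the rate was 5%.

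**What adjustment costs in precision** (SE of the session slope, unadjusted 0.0388):

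- Scenario only: 0.0393 with even choice; 0.0400, 0.0414 and 0.0443 with 25%, 50% and 75% drift to one scenario. The worst is 0.0443/0.0388 = 1.14 times the unadjusted SE.
- Scenario plus task level: 0.046, 0.056, 0.079 and 0.135 if 25%, 50%, 75% and 90% of participants stay in one scenario and climb from task 1 to 10; 0.484 if all do. If those who do not climb have tasks drawn at random from 1 to 10, the first four become 0.041, 0.047, 0.063 and 0.108.

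**Why per-task records need a session-within-participant intercept.** With k tasks per session and a share r of within-person variance common to a session, the variance of the session slope is inflated by about 1 + (k − 1)r. For k = 5 and r = 0.1 this is 1.4, and a nominal 5% test rejects about 10% of the time. For r = 10%, 30% and 50%, simulated rejection with a participant intercept alone was 10%, 20% and 27% (5 tasks) or 16%, 32% and 43% (10 tasks). With the nested intercept it was 4.7% to 5.5%.

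**The case against.** The strongest reply is that nothing is stated wrongly. The article promises only changes within persons over sessions, and the ANOVA answers that question for the programme as delivered. Model terms for an exploratory analysis can be left to an analysis plan, and the wording in Secondary Analyses is broad enough to hold a scenario term. The description of the signals as anxiety indicators comes from a passage on live monitoring and debriefing, not on a six-session trend.

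Most of this stands, and it keeps the point small. What remains is that Physiological Data names a specific, narrower method. A standard repeated-measures ANOVA does not take a covariate that changes within a person from session to session, so a plan that follows that wording inherits the gap. The link to session content covers EDA arousal events only, not HRV or EDA level. The covariates listed under Covariates and Potential Confounding Variables are baseline characteristics of the person and do not describe the stimulus.

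A reader might go further and infer that the session trend is biased, or can never be read as a changed response. The documents do not support that. Distortion of the mean trend needs systematic drift, which the design permits but does not show. Six scenarios over six sessions are compatible with an even mix throughout, and the article does not say whether task level carries over between sessions.

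It is also fair that adjustment does not fully isolate the response. Scenario choice may follow earlier arousal, and the task level reached may itself be an effect of treatment.

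**Conclusion.** The concern holds in a limited form. The ANOVA is a valid description of arousal as delivered, but its session trend should not by itself be reported as a change in anxiety response, because any drift in scenario or difficulty enters it unseparated. Size and direction are unknown. The range of 0 to 0.75 SD (0 to 3.9 SE, or 3.0 SE at the top with variable slopes) rests wholly on assumed values of R and p, and its low end is negligible. The shifts are real changes in arousal as delivered, so the significance rates above are not false-positive rates for that question. This is an optional improvement to an exploratory analysis. It does not touch the intention-to-treat analysis of SPIN or its power, and it does not concern the between-group comparison named in the same sentence of Physiological Data.

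**What to change.** In Physiological Data, aligned with Secondary Analyses, replace the ANOVA by a linear mixed model on VR-arm records:

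- Fixed effects for session number and scenario, with a participant random intercept. If per-task records are used, add a random intercept for session within participant.
- Report the unadjusted trend, labelled as delivered, beside the scenario-adjusted trend. Call both exploratory and the adjusted one descriptive.
- Add task level only in a further sensitivity model, with a note that it may be collinear with session and may respond to treatment.
- Store scenario and task labels with the signals. The article describes detecting responses during a specific task but does not say that labels are kept. Enrolment has begun, so this should be settled early.

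The cost is a change of analysis wording and the labelling. The slope SE widens slightly with scenario alone (0.039 to at most 0.044 SD under the assumed drifts) and possibly a great deal with task level (up to 0.135 SD if 90% climb through one scenario; the two cannot usefully be separated if all do). Free choice and delivery of the intervention stay as they are.

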## Methods

### Trial Design

The design is a 2-arm, statistician-blind, parallel-group RCT to test whether the VR intervention, compared with a waitlist control condition, leads to a reduction in social anxiety among youth. Assessments will be carried out at 0 (baseline, T0), 1 (posttreatment, T1), and 3 (follow-up, T2) months. A summary of the trial design can be seen in Figure 1.

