Targeted focus on social phobia: unlike general VR exposure therapy, this VR intervention is specifically designed to address social anxiety, providing immersive scenarios tailored to gradually expose participants to anxiety-inducing social situations.Autonomous VR sessions: the system operates without requiring a therapist to be physically present. If no response is detected for 30 seconds, a prompt appears asking the participant whether they need a break or would like to invite a psychologist into the session for real-time support.AI-integrated feedback system: equipped with Doubao AI, the system provides real-time prompts and encouragement based on physiological and behavioral data. For instance, if an elevated heart rate is detected, the AI may prompt: “You’re doing great! Remember the deep breathing exercise from last time? Let’s try it together—inhale for 3 seconds...exhale.”Wearable device integration: participants wear a smartwatch that tracks EDA and HRV during VR sessions. These physiological responses are monitored in real time and displayed on the back-end CP, allowing therapists or researchers to assess stress levels remotely.Gamification and reward system: this VR intervention includes a point-based system where participants earn experience points for completing tasks. These points can be exchanged for rewards, such as customizing their avatar’s appearance in the virtual world, enhancing engagement and motivation.

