### Control Group: Waitlist Control

Participants in the waitlist control group will have access to the VR intervention withheld until after the 3-month follow-up assessment. To prevent confounding effects from relevant concomitant care and interventions, participants will be required to refrain from receiving any other treatments or interventions specifically targeting social phobia during the study period. The rationale for this comparator is that this study is an early-stage RCT designed to estimate the preliminary efficacy, acceptability, feasibility, and safety of a newly developed therapist-facilitated VR intervention in a youth population in Hong Kong. Before conducting a more complex and resource-intensive active-controlled trial, it is necessary to first examine whether the intervention can be delivered as planned, whether participants can tolerate and engage with immersive exposure, and whether the study procedures, assessment schedule, and outcome measures are feasible. The waitlist design will also provide initial estimates of recruitment feasibility, adherence, dropout, outcome variability, and potential treatment signals, which can inform the design and sample size calculation of future trials. Providing delayed access also helps address ethical concerns by allowing control participants to receive the intervention after the primary assessment period.

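### The planned between-group comparison of HRV and EDA cannot be estimated, because the waitlist arm has no VR sessions during the trial

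*Protocol article*

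**What the plan says.** The Physiological Data section fixes both the source of the data and the method: "HRV and EDA data collected during VR sessions will be analyzed using repeated-measures ANOVA". It gives the analysis two aims, "repeated-measures ANOVA to examine within-subject changes across sessions and between-group differences over time". It also defines an EDA arousal event, counts such events per session, and says that their frequency and timing will be explored against session content and subjective distress.

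The Pilot Study section says when the device is worn: "participants wear a smartwatch that tracks EDA and HRV during VR sessions". The Trial Design section describes a "2-arm, statistician-blind, parallel-group RCT" with assessments at 0, 1 and 3 months. Under Control Group: Waitlist Control, the comparator participants "will have access to the VR intervention withheld until after the 3-month follow-up assessment".

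The Secondary Analyses section treats the same indicators differently. They are to be described and, if data quality allows, analysed with "repeated-measures models to explore within-participant changes across sessions" and for associations with subjective outcomes. It mentions no group contrast.

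The section on session structure adds that before each session "participants can freely choose from the 6 available VR scenarios".

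**The concern.** A between-group analysis needs observations in both groups. HRV and EDA come from a watch worn in VR sessions, and only one arm has VR sessions while the trial is running. The group comparison listed under Physiological Data therefore has nothing on the control side.

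Three things are at stake:

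- One listed analysis will give no result.
- The article gives two plans for the same data, and a reader cannot tell which one governs.
- A between-group contrast in a randomised trial reads as a treatment comparison. If it stays in the plan, readers may expect physiological evidence of VR against no VR, which this design cannot supply.

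**Working it through.** The protocol article gives no figure for the physiological analysis, so there is none to reproduce. The check is a count of which arm can supply data, and when.

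**Inputs**

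- Participants per arm: 45 (Recruitment).
- VR sessions per participant in the VR arm: 6 (Intervention Design and VR Scenarios).
- VR sessions per participant in the waitlist arm up to 3 months: 0 (Abstract; Control Group: Waitlist Control).
- Last planned assessment: 3 months (Trial Design).
- Physiological recording outside VR sessions: none described. The session-structure section, Intervention Feature 1 and the Pilot Study section all place the watch in the VR sessions. The Outcomes section says the scheduled outcomes are self-assessed online.

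**Count of session records up to 3 months**

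- VR arm: at most 45 × 6 = 270.
- Waitlist arm: 45 × 0 = 0, from 0 of 45 participants.

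**Consequence for the model**

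Write the mean for group g at session s as μ(g,s). The group effect is a contrast of μ(VR,s) with μ(waitlist,s), averaged over s. The group-by-time effect is the change in that contrast over s. With no observations for μ(waitlist,s) at any s, neither can be estimated. Only the change in μ(VR,s) across sessions can be.

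**Could the term mean other groups?**

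The randomised arms are the only groups that the article defines, and the Primary Analysis section uses the same term for the randomised SPIN contrast. The Results section mentions subgroup analyses but does not name the subgroups or link them to HRV or EDA.

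**Could there be a control recording elsewhere?**

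The EDA event rule refers to the participant's baseline without saying when it is recorded. Even if one resting recording were made in everyone at 0 months, it would give the waitlist arm a single time point and no course over sessions. The schedule figure is not legible in the copy reviewed. Its caption expands only PHQ-9, SPIN and VR.

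**The two sections side by side**

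- Physiological Data: repeated-measures ANOVA, within-subject and between-group.
- Secondary Analyses: descriptive, then within-participant repeated-measures models if data quality permits.

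Only the second can be carried out with the data that the design produces.

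**Is anything else affected?**

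The sample size rests on SPIN at 1 month. With the normal approximation, n per arm = 2 × (1.960 + 1.282)² / 0.75² = 37.4, rounded up to 38. Allowing for 15% attrition, 38 / 0.85 = 44.7, rounded up to 45 per arm, or 90 in total, as stated. HRV and EDA do not enter this calculation.

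**The case against.** The strongest reply is that little depends on this. SPIN is the primary outcome and PHQ-9 the secondary. The Expected Findings and Conclusions sections list the physiological findings as exploratory, no hypothesis refers to them, and the Secondary Analyses section already contains a feasible plan. All of that stands, and it limits the severity. It does not rescue the between-group clause.

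A reader might draw four stronger inferences, which the documents do not support:

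- **That the waitlist arm's delayed sessions will fill the gap with a non-randomised comparison.** No recording or analysis of those sessions is planned. If they were used, the groups would still be those formed by randomisation, compared as immediate against delayed delivery at different times and with further attrition. That comparison would not answer VR against no VR, but calling it non-randomised would be inaccurate.
- **That session content is ignored.** The Physiological Data section says EDA events will be explored in relation to content. The gap is narrower: the stated ANOVA has no scenario term, and nothing similar is said for HRV.
- **That difficulty rises with session number.** The article says tasks become harder within a scenario. Because scenarios are freely chosen each time, difficulty need not rise from session to session.
- **That a large share of the VR arm would be lost.** A classical repeated-measures ANOVA keeps only participants with all 6 sessions. If each session were usable with an assumed, independent probability of 0.95, 0.90 or 0.85, the complete share would be 0.95⁶ = 74%, 0.90⁶ = 53% or 0.85⁶ = 38%. The article gives no such probability, and clustering of missed sessions within participants would raise these shares. The direction of the loss is clear but its size is unknown, and the point does not depend on it.

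It can also be said that event rates and model terms are details for an analysis plan. That is fair, and they are offered below only as part of rewriting a sentence that has to change anyway.

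**Conclusion.** The point holds. As written, the between-group analysis of HRV and EDA has data from 0 of 45 waitlist participants, and it conflicts with the Secondary Analyses section. This rests on two readings of the text: that HRV and EDA are recorded only in VR sessions, and that the groups are the two randomised arms. Nothing in the article contradicts either reading.

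Severity is minor to moderate. One exploratory comparison cannot be run, while the primary SPIN analysis, the PHQ-9 analysis and the sample size are untouched. A reader should not infer that the trial's efficacy conclusions are at risk.

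**What to change.** In the Physiological Data section, delete the second aim, on group differences, and align the section with Secondary Analyses as an exploratory, within-participant analysis of the VR arm only. In the same edit:

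- Replace the repeated-measures ANOVA with a linear mixed model with a participant random intercept, fitted to all available sessions. Participants who miss a session are then kept, as in the approach already planned for SPIN and PHQ-9.
- Include session number and chosen scenario as fixed effects. Because scenarios are self-selected, this separates session from scenario only in part, and the report should say so.
- Express EDA arousal events per minute of recorded exposure. The section on adverse effects and safety procedures allows sessions to be paused or ended early, so counts per session may not refer to equal exposure.
- State that no treatment-effect claim rests on these data.

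The cost is a change of wording and slightly more analysis work. The downside is that one listed exploratory comparison is withdrawn, but it could not have been estimated. Keeping a group comparison would instead require physiological recording in both arms at common time points, which adds study procedures.
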